# Additional effect of pain neuroscience education to craniocervical manual therapy and exercises for pain intensity and disability in temporomandibular disorders: a study protocol for a randomized controlled trial

**DOI:** 10.1186/s13063-021-05532-x

**Published:** 2021-09-06

**Keywords:** Temporomandibular joint disorders, Patient education, Exercise therapy, Musculoskeletal manipulations, Chronic pain, Disability evaluation

## Abstract

**Abstract:**

The objective of this study will be to investigate the additional effect of pain neuroscience education program compared to a craniocervical manual therapy and exercises program for pain intensity and disability in patients with temporomandibular disorders (TMD). This study will be a randomized controlled trial comprising a sample of 148 participants. Subjects between 18 and 55 years, both genders, will undergo a screening process to confirm painful TMD by the Research Diagnostic Criteria (RDC/TMD), and then the volunteers will be randomized into two groups (G1: pain neuroscience education + craniocervical manual therapy and exercises vs. G2: craniocervical manual therapy and exercises). The volunteers will be recruited at the dentistry clinic. The intervention will be administered twice a week for 6 weeks by a single therapist lasting 1 h per session. The primary outcome will be pain intensity and disability and the secondary outcomes will be pain self-efficacy, kinesiophobia, and global perceived effect of improvement. The participants will be assessed immediately after the last session and at one- and three-month follow-ups. All statistical analyses will be conducted following intention-to-treat principles, and the treatment effects will be calculated using linear mixed models. The results of this study may contribute to understand the additional effect of pain neuroscience education intervention on TMD patients submitted to manual therapy and exercise.

**Trial registration:**

ClinicalTrials.gov NCT03926767. Registered on April 29, 2019.

## Background

Temporomandibular disorders (TMD) is a collective term that encompasses several clinical diagnoses involving the masticatory muscles, temporomandibular joints (TMJs), and associated structures [1]. The literature recognizes that TMD is not caused by a single factor, it is a complex disorder associated with comorbidities, physical signs and symptoms, changes in behavior, emotional status, social interactions, and changes in the function and structure of the central nervous system [2, 3].

TMD is considered the most frequent cause of chronic orofacial pain of non-dental origin, with a point prevalence of 10-15% for adults [4, 5]. In addition, there is a coexistence between TMD and neck pain [6–8], and interventions focused on the craniocervical region as a whole may contribute to decrease pain [9].

Since painful TMD has a multifactorial pathophysiology [2], there is no single approach for treating patients with TMD and the effective management of such disorder has not been established yet [10]. Several studies have demonstrated the effectiveness of interventions like manual therapy associated or not to therapeutic exercise for pain intensity and disability for TMD [9–11]. Greater effect on pain intensity for interventions focused on both orofacial and neck region against placebo/minimal intervention have been reported [9]. Most of the studies included in such systematic reviews showed small sample sizes or adopted a comparison group not submitted to an active treatment.

Current literature shows compelling evidence that the mechanistic biomedical model is not suitable to manage patients with chronic painful TMD [12]. There is a movement towards treatment modalities that encompass the biopsychosocial model that acknowledges and aims to address the biological (physical) and psychosocial factors to treat chronic pain [13, 14].

Therapeutic patient education intervention comprises the provision of information to improve the patient's understanding of their problem, speeding up the return to activities and minimizing the dependency of health professionals [15]. Pain neuroscience education (PNE) consists of a set of cognitive interventions whose main objective is to change the patient's conceptualization about pain [16]. A systematic review reported that the combination of PNE with other interventions resulted in more favorable responses for pain intensity, disability and pain catastrophizing in patients with chronic musculoskeletal disorders [17]. Moreover, pain education is the first-line recommendation in clinical practice guidelines for the management of musculoskeletal pain [18, 19].

There is no previous study published in the literature investigating the additional effect of PNE to a protocol of craniocervical manual therapy and exercises for patients with TMD. Then, the objective of our study will be to evaluate the additional effect of PNE to craniocervical manual therapy and exercises on pain intensity and orofacial disability immediately and after 1-month and 3-month follow-ups in patients with TMD. Also, as secondary outcomes, we will investigate the effect of the protocol to pain self-efficacy, kinesiophobia, and global perceived effect of improvement. The hypothesis of this study is that patients submitted to both PNE and manual therapy and exercises will show better outcomes for pain intensity and orofacial-related disability than patients submitted to manual therapy and exercises alone.

## Methods

### Trial design

This study will be a randomized clinical trial with two parallel arms, following the recommendations of the Consolidated Standards of Reporting Trials - CONSORT [20].

### Approval and registration

The study was submitted to and approved by the ethics committee for research involving human subjects of the Clinics Hospital of the Ribeirão Preto, Medical School of the University of São Paulo (HCFMRP Process N° 3449/2018). The study was registered prospectively on Clinical Trials (NCT03926767).

### Eligibility criteria and participants

A sample size of 148 female and male patients with painful TMD will participate in this study. They will be consecutively recruited from the Orofacial Pain Outpatient Clinic from the School of Dentistry of Ribeirão Preto, University of São Paulo. The study is under recruitment and the estimated study completion date is on February 2022. The inclusion criteria for participants were as follows: (i) A diagnosis of painful TMD according to Research Diagnostic Criteria for TMD (RDC/TMD) [21], (ii) history of orofacial pain at least three months prior to the study [22] and (iii) age ranging between 18 and 55 years, considering the greater prevalence associated with this age period [23].

Illiterate patients, severe depression (medical diagnoses), clinical history of tumors in the craniofacial region, patients in the post dental surgery period or submitted to previous physical therapy in the past year or to any health/pain education strategy, pregnant women, infections, whiplash-associated disorders and with chronic degenerative inflammatory or neurologic disorders were excluded from this study. Patients will be instructed to not use pain relief medications during the intervention period of this trial and if any medication be used, participants will be encouraged to report. All participants will be informed about the procedures of this study, will have to report agreement to participate, and will sign the consent form. Participants will be instructed that they will be free to remove consent at any time of the study.

### Analysis of the population

In the event of two consecutive absences from treatment sessions, patients will be contacted by telephone. The analysis will follow the intention-to-treat principles. An intention-to-treat analysis will be performed using the patient’s most recent assessment in case of withdrawals or absence of data. Possible adverse effects (injuries) occurring during the intervention period, the individuals will be referred for appropriate treatment.

### Procedures, randomization, and allocation

Once the patient has accepted the invitation to participate and signed the formal consent to participate, one researcher will run the assessment to determine eligibility. After this initial assessment, participants will be randomly assigned following simple computerized randomisation procedures to one of the two treatment groups through the use of cards previously placed in opaque sealed envelopes: G1 – Pain Neuroscience Education + craniocervical manual therapy and exercises or G2 - craniocervical manual therapy and exercises. The allocation sequence will be generated by a researcher not involved in the assessment and interventions ([name]), and another research assistant will assign participants to interventions (Fig. 1). Figure 1 shows the trial procedure, and Table 1 illustrates the trial schedule.

**Fig 1 Fig1:**
[figure not shown]
Flow chart demonstrating the randomization process to be adopted in the present study. PNE, pain neuroscience education; MT, manual therapy; NMC, neck motor control exercises

**Table 1 Tab1:**
[figure not shown]
Recommended protocol items: schedule for enrollment, interventions, and assessments

*PNE* = pain neuroscience education, *HADS* = Hospital Anxiety and Depression Scale, *PCS* = Pain Catastrophizing Scale, *CF-PDI* = Cranio Facial Pain and Disability Inventory, *PSEQ*= Pain Self-Efficacy Scale, *TSK/TMD* = Tampa Scale for Kinesiophobia for Temporomandibular Disordes, *NPQ =* Neurophysiology of Pain Questionnaire, *GPE* = Global Perceived Effect, *EARS* = The Exercise Adherence Rating Scale

One blinded researcher regarding treatment group allocation will run the assessments pre-treatment, immediately after and at 1-month and 3-month follow-ups. The evaluations of the study will be carried out according to the recommendations of the Initiative on Methods, Measurement and Pain Assessment in Clinical Trials (IMMPACT) for chronic pain [24].

During the assessment for eligibility, the participants will be assessed according to RDC/TMD to confirm the presence of TMD [21]. Afterwards, the participants will answer the Pain Numeric Rating Scale (NPRS) [25], The Craniofacial Pain and Disability Inventory (CF-PDI) [26], Global Perceived Effect (GPE) of improvement [25], Tampa Scale for Kinesiophobia for Temporomandibular Disorders (TSK/TMD )[27], Pain Catastrophizing Scale (PCS) [28], Pain Self-Efficacy Questionnaire (PSEQ) [29], Revised Neurophysiology of Pain Questionnaire (NPQ) [30], and Hospital Anxiety and Depression Scale (HADS) [31]. This protocol followed the Standard Protocol Items: Recommendations for Interventional Trials (SPIRIT) recommendations [32].

### Baseline assessment

#### Hospital anxiety and depression scale (HADS)

HADS [33] will be employed to identify anxiety disorders and depression. It was translated and validated into Brazilian Portuguese. The HADS is divided into the anxiety subscale (HADS-A) and the depression subscale (HADS-D), both containing seven interspersed items. It is composed of seven items for depression and seven items for anxiety, each item including four response options ranging from 0 to 3. A cutoff of ≥8 was described with good sensitivity and specificity values (0.70–0.90) for anxiety and depression symptoms [31].

#### Pain Catastrophizing Scale (PCS)

The PCS Brazilian Portuguese [28] is a self-administered questionnaire that consists of 13 items for the assessment of catastrophizing thoughts. It is divided into three domains: helplessness, magnification, and rumination. Each item is scored on a 5-point ordinal scale. The B-PCS total score ranges from 0 to 52 points, higher values denote greater pain catastrophizing. Acceptable values for validity, internal consistency, and test-retest reliability are described for the Brazilian PCS [28].

### Primary outcomes

#### Pain intensity

The NPRS [25] will be used to assess pain intensity in this trial and consists in a sequence of numbers from 0 to 10, in which 0 represents “no pain” and 10 represents “worst pain imaginable” [25].

#### Orofacial and pain disability

The Craniofacial Pain and Disability Inventory (CF-PDI) [34] is a self-administered questionnaire that measures the outcomes of pain and disability related to craniofacial pain and demonstrated an acceptable structural validity, internal consistency, reproducibility, and construct validity [34]. Also, the Brazilian Portuguese version showed acceptable measurement properties [26]. It consists of 21 items, with a score ranging from 0 to 63 points. Each question is scored on a 4-point ordinal scale, ranging from 0 to 3. A higher score reflects higher disability levels.

### Secondary outcome measures

#### Pain Self-Efficacy Questionnaire -PSEQ

Study participants will be evaluated on self-efficacy related to chronic pain, which can be defined as an individual’s confidence he/she can successfully produce desirable results related to living with chronic pain. The PSEQ has 10 items which are rated on a 7-point ordinal scale (ranging from 0: “*not at all confident*” to 6: “*completely confident*”). It was adapted and validated to Brazilian Portuguese [29]. Previous research showed an effect on self-efficacy using a PNE intervention based on metaphors compared to an intervention using cognitive-behavioral concepts [35].

#### Tampa Scale for Kinesiophobia for Temporomandibular Disorders - TSK/TMD

The TSK/TMD is a self-report questionnaire that assesses the fear of movement [36]. In this study, the TSK-TMD with 12 items validated in Brazilian Portuguese was used [27] and showed acceptable psychometric measurements. Each item is scored on a 4-point ordinal scale, ranging from “strongly disagree” (score = 1) to “strongly agree” (score = 4). Ratings are summed to yield a total score. Higher scores reflect a greater fear of movement (12–48 points).

### Participant ratings of Global Perceived Effect - GPE

The GPE of improvement used for this trial is an 11-point scale that ranges from − 5 (“vastly worse”) through 0 (“no change”) to + 5 (“completely recovered”) and participants are asked: “*Compared to when this episode first started, how would you describe your orofacial pain these days*?”. A higher score indicates higher perception of recovery from the condition [25].

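### The GPE item asks about change since the pain episode began, so follow-up scores include pre-trial course; the pre-treatment GPE should be a covariate and only the adjusted between-group difference interpreted

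*Protocol article*

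**What the plan says.** The section on participant ratings of Global Perceived Effect describes an "11-point scale that ranges from − 5 (“vastly worse”) through 0 (“no change”) to + 5 (“completely recovered" and prints the question: "Compared to when this episode first started, how would you describe your orofacial pain these days". It reads the result as follows: "A higher score indicates higher perception of recovery from the condition".

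The eligibility section requires a "history of orofacial pain at least three months prior to the study" and sets no maximum duration. The Abstract gives the treatment length: "The intervention will be administered twice a week for 6 weeks by a single therapist".

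The Background makes the GPE a secondary outcome: "we will investigate the effect of the protocol to pain self-efficacy, kinesiophobia, and global perceived effect of improvement".

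The text after Table 1 says that a blinded researcher "will run the assessments pre-treatment, immediately after and at 1-month and 3-month follow-ups". It lists "Global Perceived Effect (GPE) of improvement" among the questionnaires answered after the eligibility examination.

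The Data analysis section plans linear mixed models for all outcomes, to give both mean effects of the interventions and group differences. Time consists of post-intervention and follow-up. The covariates are psychosocial variables, the pain neurophysiology knowledge score, sex, ethnicity and age. The pre-treatment GPE is not among them.

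**The concern.** The item and the objective refer to different periods. The objective concerns what the treatment does, while the item asks for the whole course since onset. A participant who worsened before entry and then improved under treatment can still answer zero or below. One who had partly improved before entry can score above zero with no change in the trial.

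Two things are at stake. First, differences between participants in their course before entry add variation to the follow-up GPE that has nothing to do with allocation, which can widen the confidence interval for the group difference. Second, the plan reports mean effects per intervention, and a raw arm mean on this item is perceived course since onset, not change during treatment.

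**Working it through.** **Plan's own figure.** The protocol gives no standard deviation, target difference or power for the GPE, so there is nothing to reproduce for this outcome. The sample size rests on pain intensity and disability. The disability figure does reproduce: f = 0.25, two-sided 5% and 80% power give 127.5 in total, hence 128, or 64 per group. It does not bear on the GPE.

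**Share of the recalled period that precedes treatment.** Inputs: at least 3 months of pain before entry (eligibility section), 6 weeks or about 1.5 months of treatment (Abstract), and follow-ups at 1 and 3 months, taken here as counted from the end of treatment. I also assume that treatment starts soon after entry and that the patient regards the qualifying history as one episode. At the shortest permitted history:

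- Post-treatment: 3 / (3 + 1.5) = 0.67
- 1 month: 3 / (3 + 2.5) = 0.55
- 3 months: 3 / (3 + 4.5) = 0.40

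Longer histories raise each share, and no upper limit is stated. The shares describe time, not how much of the score comes from each part.

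**Effect on the group difference.** Write follow-up GPE = P + C, where P is perceived change from onset to entry and C is perceived change during the trial. P is fixed before allocation, so its expected difference between arms is zero and the contrast estimates the effect on C without bias.

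Let r = SD(P)/SD(C) and ρ = corr(P, C). Relative to an item that measured C alone, the standard error is multiplied by √(1 + r² + 2ρr).

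For illustration only, take ρ = 0, an effect of 0.5 SD of C and 64 per arm:

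| r | SE multiplier | Power | n per arm for 80% power |
|---|---|---|---|
| 0 | 1.00 | 81% | 63 |
| 0.5 | √1.25 = 1.12 | 72% | 79 |
| 1 | √2 = 1.41 | 52% | 126 |

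These figures depend entirely on r and ρ, and the protocol gives neither. If ρ = −r/2, the multiplier is √(1 + r² − r²) = 1 and the loss disappears. A negative ρ is plausible because the scale is bounded: someone already improved at entry has less room to improve further.

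**What adjustment does.** If R is the correlation between pre-treatment and follow-up GPE, using the pre-treatment score as a covariate multiplies the residual variance by about 1 − R². In the ρ = 0, r = 1 case with P measured exactly, R² = r²/(1 + r²) = 1/2, so the variance falls from 2 to 1 in units of Var(C) and the whole loss is recovered. With an imperfect pre-treatment rating, part of it is recovered. If R is near zero, the adjustment costs about one degree of freedom.

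**The case against.** The strongest defence is that nothing here is an internal error. The protocol reads the score as recovery from the condition, which fits an onset anchor, and takes the item from a cited source. The trial's question is the additional effect of pain neuroscience education, a between-arm contrast that randomisation protects. The GPE is secondary, so the primary analyses and the sample size are untouched. All of this stands.

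The defence also says that a baseline covariate for one outcome is commonly left to the analysis plan, and that Table 1 is not shown, so the timing of the GPE rests on the text alone. That limits the point but does not remove it. The article itself names the covariates, and the text lists a pre-treatment GPE that would serve.

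Three stronger readings are tempting and are not supported:

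- **That the arm comparison is biased.** Pre-trial course is balanced in expectation.
- **That the loss of precision can be given a figure.** A reader might assume an SD of 2 for change during the trial and an independent SD of 1 to 2.5 for the course before it, and get √(1 + 1/4) = 1.12 to √(1 + 6.25/4) = 1.60. No such SD is in the protocol. The upper end implies a total SD of √(4 + 6.25) = 3.20, wider than a uniform spread over all 11 points (√10 = 3.16). Independence is doubtful too.
- **That anchoring the item to the start of treatment would turn arm means into treatment effects.** Both arms are treated actively and there is no untreated arm, so natural course and regression to the mean would remain in each arm mean under any anchor.

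**Conclusion.** The point holds in limited form. The item is anchored to onset, nothing in the protocol re-anchors it, and follow-up scores therefore include at least three months of pre-trial course, provided patients treat the qualifying history as the episode. A reader might infer years of earlier course, but the document says only at least three months without an upper limit.

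The consequence is a loss of precision for the between-arm GPE comparison, of a size the document does not determine, and raw arm means that do not measure change during treatment. There is no bias in the randomised contrast. The planned covariates leave out the one listed measurement best placed to absorb the unwanted variation. This is a low-cost improvement to a secondary analysis, not a defect that threatens the trial's main conclusions.

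**What to change.** Keep the cited wording and the pre-treatment GPE. In the linear mixed model for the GPE, add each participant's pre-treatment GPE as a covariate, with the post-intervention and follow-up scores as responses. State that only the adjusted between-group difference is read as the effect of adding pain neuroscience education, and that raw arm means describe perceived course since onset.

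The cost is one covariate and one sentence on interpretation, using a measurement the protocol already lists. Before fixing the model, confirm against the assessment schedule that the GPE is in fact collected before treatment.

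Do not change the question mid-trial or drop the pre-treatment score. The study started in April 2019, with completion given as February 2022, so a new wording would leave two non-equivalent scores split by calendar time. Dropping the pre-treatment score would leave later participants without the covariate and rule out a single adjusted model.

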#### The revised Neurophysiology of Pain Questionnaire - NPQ

The NPQ is a self-administered instrument to assess the knowledge regarding pain neurophysiology. The questionnaire will be administered to quantify the level of knowledge of the participants after the PNE program. Each item has the following response options: true (1 point), false (0 point), and undecided (0 point). The maximum score is 12 points in the revised version. The NPQ showed acceptable internal consistency and good test-retest reliability [37]. There is a cross-culturally version of the NPQ to Brazilian Portuguese [30].

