#### The Exercise Adherence Rating Scale - EARS

EARS is a patient-reported outcome measure composed of six items that directly assess adherence behavior. In the present study, it will be used to assess the perception of adherence to prescribed home exercises. It was translated and validated into Brazilian Portuguese [38]. The six items should be summed and items with positive phrases are reversely scored, meaning items 1, 4, and 6. The six items are scored using an ordinal Likert scale of possible answers (0 = strongly agree to 4 = totally disagree), with higher scores indicating greater adherence (0 to 24). Participants will answer the EARS only at the end of the treatment, to assess retrospectively the adherence behavior.

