### Data analysis

The mean effects of the interventions and the group differences for all outcomes (primary and secondary) will be calculated using linear mixed models, incorporating terms for the treatment groups, time (post-intervention and follow-up), and interaction terms (treatment subgroups and time) as well as, psychosocial variables, knowledge about pain neurophysiology (score on the NPQ), sex, ethnicity, and age as covariates. Secondary analysis will be conducted using regression models to determine whether baseline scores of psychosocial variables (HADS, PCS, TSK/TMD) will moderate the effect of treatments. All data will be double entered prior to the analysis. The analysis will follow the intention-to-treat principles. Additionally, we will adopt analysis per protocol excluding patients that did not complete the 6 weeks of treatment. The statistician will receive coded data and will be blinded to the participants’ allocation groups. The data collected will be stored coded to protect patient confidentiality. In order do to handle missing data, we will replace the value by the last observation carried forward. For all analysis, we will use the IBM SPSS software package, version 22 (IBM Corp, Armonk, NY) and the significance level will be established at 0.05.

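### The written NPQ scoring rule credits the answer *true* on every item, so followed literally it counts agreement rather than pain knowledge (low severity; a one-sentence correction)

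*Protocol article*

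**What the plan says.** In the protocol article, the section on the revised NPQ gives the purpose, the scoring rule and the maximum together:

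- Purpose: "The NPQ is a self-administered instrument to assess the knowledge regarding pain neurophysiology".
- Item rule, for each item: "true (1 point), false (0 point), and undecided (0 point").
- Maximum: "The maximum score is 12 points in the revised version".
- Use in the trial: "The questionnaire will be administered to quantify the level of knowledge of the participants after the PNE program".

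The Data analysis section gives the score a second use. The linear mixed models for all primary and secondary outcomes include "knowledge about pain neurophysiology (score on the NPQ), sex, ethnicity, and age as covariates", together with psychosocial variables.

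No other section restates or corrects the item rule. The article shows neither the NPQ items nor their answer key.

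**The concern.** A knowledge score should reward the right answer. The written rule rewards one response option and does not mention correctness. On an item whose statement is false, a participant who rightly rejects it gets 0, the same as someone who is undecided, while a participant who wrongly accepts it gets 1.

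Two uses of the score are at stake. The NPQ is the only listed measure of whether participants took in the content of the pain neuroscience education (PNE), which is the component under test. A score that mixes knowledge with a tendency to agree is a weaker check of that. The same score is also a covariate in the models for every outcome, and there it would not measure the knowledge it is named for.

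**Working it through.** **Inputs**

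- Points per item: *true* 1, *false* 0, *undecided* 0 (NPQ section).
- Maximum score: 12 (NPQ section).
- Number of items: not stated. Assumed to be 12, each worth one point.
- k, the number of items whose correct answer is *false*: not stated. Possible range 0 to 12.

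**Step 1: the stated maximum.** 12 items × 1 point = 12, which agrees with the article. Scoring one point per correct answer also gives 12 × 1 = 12, so the maximum cannot show which rule is meant.

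**Step 2: two limiting respondents.**

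- Rule as written (score = number of *true* answers): an all-*true* respondent scores 12 for any k. A fully informed respondent scores 12 − k.
- Scoring by key (score = number of correct answers): an all-*true* respondent scores 12 − k. A fully informed respondent scores 12 for any k.

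| k | As written: all-*true* | As written: informed | By key: all-*true* | By key: informed |
|---|---|---|---|---|
| 0 | 12 | 12 | 12 | 12 |
| 2 | 12 | 10 | 10 | 12 |
| 4 | 12 | 8 | 8 | 12 |
| 6 | 12 | 6 | 6 | 12 |

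The two rules agree only at k = 0. These respondents are extremes that show the direction of the fault. They do not estimate any difference between the arms.

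**Step 3: an illustrative gain in knowledge.** Suppose the chance of a correct answer rises from 0.4 to 0.7 on every item, with no *undecided* answers. These probabilities are assumed, not taken from the article.

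- By key: gain = 12 × 0.3 = 3.6 points for any k.
- As written: each true statement gains 0.3 and each false statement loses 0.3, so gain = (12 − k) × 0.3 − k × 0.3 = (12 − 2k) × 0.3.

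| k | Gain as written | Gain by key |
|---|---|---|
| 0 | 3.6 | 3.6 |
| 2 | 2.4 | 3.6 |
| 3 | 1.8 | 3.6 |
| 4 | 1.2 | 3.6 |
| 6 | 0.0 | 3.6 |
| 7 | −0.6 | 3.6 |

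In this illustration the literal score understates the gain for k from 1 to 5, shows none at k = 6, and turns negative only when more than half the items are keyed *false*.

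**Step 4: is k = 0 plausible?** The article cannot settle this. Against it, *false* is offered as an answer separate from *undecided*, yet under the rule it could never be right. The article also states item direction where another scale needs it: for the Exercise Adherence Rating Scale, "items with positive phrases are reversely scored, meaning items 1, 4, and 6". Nothing comparable is given for the NPQ.

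**The case against.** The best defence is that this is a short summary of an existing instrument with cited validation work, and that the sentence is loose wording for one point per correct answer. An article need not reproduce an item key, and staff may well score by the instrument's own key. As an account of the cause this is probably right. It does not rescue the sentence. The article did not leave scoring to the cited source: it stated a rule, and that rule conflicts with the purpose given in the same section.

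Four stronger readings are tempting, and the document does not support them.

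- *The knowledge check would be reversed.* In the equal-gain illustration that needs k above 6, and k is not given.
- *The PNE syllabus proves that some items are false.* One of its 17 topics deals with mistaken ideas about pain, but nothing says the NPQ tests that topic or how such items are worded. A misconception can also be tested with a true statement.
- *Forms already collected have been mis-scored.* Recruitment began in April 2019, so forms may exist, but nothing shows how they were scored.
- *The treatment effect on the primary outcomes is biased.* Poor measurement of one covariate in a randomised comparison mainly costs precision, and no bias from the scoring rule is shown. If the covariate is the score after PNE, adjusting for something that treatment changes is a separate question, which scoring by key would not cure.

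It also stands that the Abstract and the objectives in the Background name neither a primary nor a secondary outcome based on the NPQ.

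**Conclusion.** The point holds as a misstated scoring rule of low severity. Read plainly, the rule makes the NPQ score a count of *true* answers. It contradicts the stated aim of measuring knowledge unless every item is a true statement, which the document does not show and which is unlikely.

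If the rule were applied literally, the knowledge check after PNE would be weakened and the covariate "knowledge about pain neurophysiology (score on the NPQ") would be mis-measured. The amount cannot be computed here: the tables above rest on an assumed 12 one-point items and an unknown k, and the gains also on assumed probabilities. Pain intensity, disability and the sample size calculation do not use the NPQ score, so the primary outcome scores and the planned numbers are unaffected.

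**What to change.** Replace the scoring sentence with a statement that each NPQ item scores 1 when the response matches the instrument's answer key and 0 when it is wrong or undecided. The maximum of 12 is unchanged.

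Confirm how the forms already collected were scored. If the key was used, the wording correction is enough. If the literal rule was used, rescore from the stored item responses before the score is used as a covariate or as a check of PNE uptake.

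The cost is one sentence and one query to the data team, plus a simple recalculation only if the literal rule was used. Participants are not affected.
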